## Background

Patient safety is a key concern amid continuous efforts to improve the effectiveness and efficiency of health systems [1]. Defined as the “reduction of risk of unnecessary harm associated with health care to an acceptable minimum” [2] (p. 19), patient safety refers to the presence or absence of adverse events and/or medical errors and serves to compare the performance of health facilities worldwide [3]. Patient safety is strongly related to different nurse activities, particularly those where clinical decisions must be made [4, 5]. Clinical decision-making has been defined as “a contextual, continuous, and evolving process, where data are gathered, interpreted, and evaluated in order to select an evidence-based choice of action” [6] (p. 401).

Decision-making is a frequently performed process in emergency departments, especially in the course of triage, when nurses sort patients by care priority based on a process that aims for the best allocation of human and physical resources. It remains a human-driven process and as such is prone to error. Errors in clinical decisions can have serious consequences for patient safety [7, 8]. Underestimating the severity of a patient’s condition can lead to delayed emergency care and medical treatment that decreases the quality of the intervention [9]. Overestimating a patient’s condition results in inadequate resource allocation, which leads to overcrowding and work overloads in specific units [10]. With this in mind, nurses must arrive at highly reliable decisions and limit the occurrence of errors. What is more, nurses who perform triage must not only reach accurate decisions, they must also do so rapidly [11–13]. Indeed, decisions must be made within a very short time lapse (< 5 min) based on limited information and with limited access to peer clinical supervision [11, 14, 15].

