To support nurses during the ED triage process and reduce errors, various scales have been developed since the early 1990s. Today, most of the existing triage scales cover four or five emergency levels [16–18]. Following these international standards, the Swiss Society of Emergency and Rescue Medicine currently recommended using the Swiss Emergency Triage Scale or SETS® [19] for ED patient triage. The SETS® has been psychometrically validated [10, 20] and is widely used in Switzerland, France, and Belgium. It spans four emergency levels from 1 to 4: acute, urgent, semi-urgent, and non-urgent. The introduction of triage scales has standardized nurse decisions and has facilitated the study of triage quality. Triage quality is most commonly assessed according to one indicator: accuracy. The accuracy of nurse triage decisions is measured by the degree of agreement between the emergency level assigned and a gold standard set by a panel of experts [21]. When nurses assign a level higher than the gold standard, it is referred to as overtriage [22, 23]. When the assigned level is lower, it is referred to as undertriage [9, 24].

In their systematic review, Farrohknia et al. [25] found the level of accuracy of nurse emergency level assignments to be medium to low. There has been little research, however, into the reasons for this relatively poor performance. The few studies that have investigated the issue have done so from the angle of nurse individual factors and contextual factors [26–28]. The individual factors considered include characteristics specific to nurses such as personality (flexibility, decision-making autonomy), cognitive processes (critical thinking, prompt decision-making), behavioral processes (working under pressure, being organized), and nurse experience (confidence in one’s decision-making) [28–30]. Where contextual factors are concerned, researchers have focused on the numerous distractors present in the environment [31–34], specifically frequent task interruptions, noise, and variable workloads. Any of these can result in the delayed performance of care activities, information loss, and a drop in concentration that alters the decision-making process, particularly when performing complex activities.

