The organization component refers to management style and time management, available resources, social relationships, and rules and procedures in place [45]. Nurse triage guidelines mention constraints that bear upon the task, especially limited time [61, 62]. Two studies [49, 63] carried out in European ED have demonstrated the mean duration of nurse triage to be 4 min. In our study, the time required by the nurses to determine the triage score for each clinical vignette will be measured and the variable will be considered in the analyses.

Though the SEIPS model focuses on the work system dimension, it also allows examining the dimensions of process and outcomes. The process dimension informs on the reasoning used by nurses to arrive at clinical decisions [64]. Within the framework of our study, there will be no in-depth examination of the decision-making process per se, only of the final outcome, that is, the SETS® scores (i.e., emergency level) that nurses assign to patients. Finally, the outcomes dimension will be analyzed in terms of accuracy of assigned emergency level. The pilot study will not examine the outcomes dimension in connection with employees and the organization.

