### Instruments

Sociodemographic data, both personal (gender, age, family situation) and professional (employment status, total number of years of experience, number of years in current department), will be collected through a questionnaire developed on the basis of elements gathered in previous studies of triage accuracy [27, 35, 72].

The clinical decision-making of the nurse participants will be judged on the emergency level that they assign based on the SETS® criteria. Following their clinical reasoning, nurses assign patients an emergency level from 1 to 4. The scale has been the focus of various independent studies [20, 73] where computerized clinical vignettes were used with ED nurses and paramedics.

Nurse level of confidence in their clinical decision-making will be measured using a visual analogue scale from 0 to 100 [74]. This scale will be presented to nurses after each emergency level assignment. The question asked will be: “Now that you have completed this clinical vignette, how confident are you of the emergency level that you have assigned?” Nurses will rate their confidence from 0 to 100, with 0 corresponding to “I am not at all confident of my decision” and 100 to “I am fully confident of my decision.” Visual analogue scales allow measuring the intensity of a subjective experience and are widely used in clinical settings [66]. In a study where the scale was used by 69 nurses in a triage situation, the researchers reported no problems with its utilization [35].

The feasibility of the SG will be assessed on the basis of criteria drawn from Sidani and Braden [44] and Feeley et al. [75], including accessibility of target population, appropriateness of inclusion and exclusion criteria, participation rate, withdrawal rate after starting SG, presence and frequency of problems during delivery of SG (understanding, utilization, clarity), presence and frequency of missing data and outliers, and participant satisfaction with SG.

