### Data analysis plan

The nurse participants (expected *N* = 80) will be the analysis units for the descriptive analyses, and the assigned triage scale scores will be the analysis units for the correlational analyses and some descriptive analyses (number of nurses multiplied by number of vignettes—expected *N*: 80 × 20 = 1600). The following data analysis plan will be carried out to answer the research questions: First, the collected data will be verified (compliance with inclusion criteria, identification of missing data and outliers). Second, the data on the nurses (sociodemographic and professional) will be analyzed via descriptive statistics, both univariate (mean, median, standard deviation, interquartile range, and absolute and relative frequency) and bivariate (contingency table and marginal frequency). Third, triage accuracy will be measured by the level of agreement between the answers given by the nurses and the gold standard established by the experts. For each nurse, the scores assigned to each clinical vignette will be compared against the gold standard. The results of the comparison will be a three-level multinomial variable: accurate triage (nurse score same as gold standard), overtriage (score higher than gold standard), and undertriage (score lower than gold standard). Over- and undertriage frequencies will be used to describe the triage accuracy of the four groups, that is, the control group and the three experimental groups: noise (A), task interruptions (B), and noise and task interruptions (C). Fourth, to examine the individual and combined effects of the distractors on the triage accuracy of the nurse participants, the groups will be compared against one another using a random-intercept multinomial regression model. For all the analyses, the statistical significance level will be *p* ≤ 0.05. All the data will be analyzed using the R statistical software [79].

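### The over/undertriage rule, applied to the numeric SETS score as written, reverses the direction of every discordant decision because SETS runs from 1 (acute) to 4 (non-urgent)

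*Protocol article*

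**What the plan says.** All places are in the protocol article.

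- **Data analysis plan.** Each nurse's score is compared with the expert gold standard and becomes a three-level variable: accurate, "overtriage (score higher than gold standard), and undertriage (score lower than gold standard"). This variable is used twice: for the over- and undertriage frequencies of the four groups, and as the outcome of the random-intercept multinomial regression that compares the groups.
- **Background, on the scale.** "It spans four emergency levels from 1 to 4: acute, urgent, semi-urgent, and non-urgent".
- **Background, on the two errors.** "When nurses assign a level higher than the gold standard, it is referred to as overtriage". "When the assigned level is lower, it is referred to as undertriage".
- **Theoretical framework.** Score and level are equated: "the SETS® scores (i.e., emergency level) that nurses assign to patients".
- **Instruments.** The recorded response is a number: "nurses assign patients an emergency level from 1 to 4".
- **Background, on the clinical meaning.** "Underestimating the severity of a patient’s condition can lead to delayed emergency care", whereas "Overestimating a patient’s condition results in inadequate resource allocation".

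**The concern.** The scale counts downwards in urgency: the most urgent patient has the smallest number. The derivation rule speaks of a higher or lower score. Read as a comparison of numbers, it calls a decision overtriage exactly when the nurse judged the patient less urgent than the experts did. That is undertriage in the clinical sense that the Background sets out.

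The direction of error is part of what the study reports, because over- and undertriage are two of the three levels of the modelled outcome. If the rule is programmed literally, a distractor that mainly leads nurses to underestimate severity would be reported as one that mainly leads them to overestimate it, and the reverse. Nothing in the output would give this away, since totals, accuracy rates and model fit would look normal. The article also intends the results to inform a larger study.

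**Working it through.** **Inputs**

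- SETS levels: 1 acute, 2 urgent, 3 semi-urgent, 4 non-urgent (Background).
- Rule: over if score > gold, under if score < gold (Data analysis plan, read numerically).
- Planning values: accuracy 0.85 in control, a decline of 0.1 in the experimental groups, intraclass correlation at most 0.03, 20 nurses per group, power at least 0.80 (Population and sampling).
- 20 vignettes per nurse and significance at 0.05 (Data analysis plan). The test is assumed to be two-sided, as sidedness is not stated.

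**Step 1. The plan's own figure.** The article obtained 20 per group by simulation. A closed-form check agrees.

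- Two proportions, 0.85 against 0.75, two-sided 0.05, power 0.80: 250 decisions per group.
- Design effect: 1 + (20 − 1) × 0.03 = 1.57.
- Nurses per group: 250 × 1.57 / 20 = 19.6, so 20.
- Effective size with 20 nurses: 400 / 1.57 = 254.8, which gives power 0.807.

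This calculation uses only accurate against inaccurate, so the direction of error does not enter it.

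**Step 2. All possible pairs.** Each cell gives the label from the numeric rule, then the label by urgency.

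| Gold | Assigned 1 | Assigned 2 | Assigned 3 | Assigned 4 |
|---|---|---|---|---|
| 1 | accurate / accurate | over / under | over / under | over / under |
| 2 | under / over | accurate / accurate | over / under | over / under |
| 3 | under / over | under / over | accurate / accurate | over / under |
| 4 | under / over | under / over | under / over | accurate / accurate |

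Of 16 pairs, 4 are concordant and keep their label. All 12 discordant pairs change: 6 labelled over are undertriage, and 6 labelled under are overtriage. For example, if the gold standard is 1 and the nurse assigns 3, severity is underestimated, yet 3 > 1 makes it overtriage under the rule.

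**Step 3. How many decisions this touches.** With every vignette completed, each group has 20 × 20 = 400 decisions.

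- Control: (1 − 0.85) × 400 = 60 discordant.
- Each experimental group: (1 − 0.75) × 400 = 100 discordant.
- Total: 60 + 3 × 100 = 360 of 4 × 400 = 1600, or 22.5%.

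**Step 4. What changes in the results.** Suppose a share u of the 360 discordant decisions is truly undertriage. The true count is 360 × u and the reported count is 360 × (1 − u). These agree only when u is one half. The article gives no value for u, so the distortion in the frequencies cannot be sized further.

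In the multinomial model, take accurate triage as the reference category (an assumption, as the article does not name one). The two remaining contrasts exchange names. Swapping labels is a one-to-one relabelling, so the fit and the overall group test stay the same, provided the random intercepts treat the two error categories alike.

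**The case against.** The strongest reply is that higher is meant in the everyday sense: a higher emergency level is a more urgent one. The Background uses the word this way in the same paragraph that numbers the scale, and its account of over- and underestimation fits that sense. Because the Theoretical framework equates score with level, the rule in the Data analysis plan can be read the same way, and then all the sections agree. This is probably what the authors intend. It does not settle the matter: the operational rule says score, the recorded response is a number from 1 to 4, and no sentence says that higher means more urgent or that the scale is reverse-coded.

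A second reply is that the swap depends on how the variable is programmed. The article says that game data are recorded automatically, but not how levels are stored or compared. The initiator of SETS development also helps to build the vignettes, so a reversal might well be noticed. This stands. The error is conditional on literal coding and cannot be presented as certain to occur.

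A third reply concerns the reach of the problem. The primary question and hypotheses 2 to 5 are about accuracy and inter-rater reliability, with none directed at over- against undertriage. This also stands. A reader might infer that the primary accuracy result would be reversed, or that the sample size is affected. The article does not support either inference, because the accurate category is untouched and the power calculation uses only the accuracy rate. A reader might also infer that an unsafe error would be passed off as a harmless one. The Background does not treat overestimation as harmless: it links it to crowding and excess workload.

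**Conclusion.** The rule as stated conflicts with the scale as stated, and following it literally gives the wrong direction for every discordant decision. This is not detail left to a separate analysis plan, because the article fixes both the rule and the numbering.

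The figure of about 360 in 1600 is the expected number of discordant decisions, not an estimate of bias. It assumes literal numeric coding, all 20 vignettes completed by every nurse, and 75% accuracy in each experimental group. Play stops at 2 h even if vignettes remain, which would lower the count. Hypothesis 3 expects the combined-distractor group to do worse than the single-distractor groups, which would raise it.

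What is at risk is the direction of error in the group frequencies and in the two non-reference contrasts. Relabelling would repair the output if the reversal were noticed, but a reader working from the published rule could not tell which coding had been used.

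**What to change.** In the Data analysis plan, define the categories by urgency and by number:

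- overtriage: the assigned level is more urgent than the gold standard, that is, a smaller SETS number;
- undertriage: the assigned level is less urgent than the gold standard, that is, a larger SETS number.

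Replace higher and lower in the Background definitions with more urgent and less urgent, so that the two sections agree. Before analysis, check the derivation code against one known case, such as gold 1 with assigned 3, which must come out as undertriage.

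The cost is a sentence or two of text and one line of code to confirm. Data collection, sample size and model are unaffected.

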### Ethical considerations

Each nurse from the emergency units selected for the study will receive a written information letter explaining how the study will be conducted, what their participation entails, and what data protection measures will be taken. Each nurse will then be able to take all the time they need to decide whether to participate in the study, without the decision having any consequence whatsoever for their career. The research team will have access only to anonymous data. All data will be deleted after data analysis. To participate in the study, the nurses will have to sign a consent form, which will be stored in accordance with the recommendations of the Swiss Human Research Ethics Board (Canton of Vaud, Switzerland). The time that the nurses spend evaluating the clinical vignettes with the SG will count as work hours.

## Discussion and conclusion

Triage is considered a dynamic and complex nursing activity that requires a high level of concentration in a work environment marked by frequent task interruptions, an unpredictable workload, and a noisy physical layout [80]. These three elements may influence the accuracy of the emergency levels that nurses assign to patients [32, 52]. Our research project will seek to test the effects of distractors on triage accuracy through the use of an SG that simulates the ED environment. The project will overcome many limitations of previous studies by accounting for a distractive environment and providing a safe setting for patient triage assessment. The results of our study will inform the design of a follow-up large-scale study that will not only unscramble the impact of distractors on the triage process but also identify sociodemographic factors that may play a role in triage accuracy. This could provide emergency units with critical information that will allow them to adapt the work environment and allocate health workers more efficiently and effectively.

Today’s technological advances have made it possible to create tools such as SG to optimize the learning and evaluation processes in many different fields. The most salient success stories so far have perhaps been in medicine and aviation. SG, such as the one that we are developing and studying, are tools that hold tremendous promise not only to help us better understand triage accuracy and the impact of distractors but also to help us benchmark the triage process and improve its quality. They may also be used in education and ED training as a complement to written scenarios and in-person simulations.

In experimental investigations, SG allow collecting a wide array of precise measurements, maintaining full control of simulated events, modulating parameters with rigor, measuring performances in detail, and controlling trigger events better [78]. SG, as presented here, have considerable advantages for simulation and empirical research. All their benefits, however, must rely on a strong methodological design [81]. Based on the analysis of 12 studies that evaluated the effects of task interruptions on health activities, Sanderson and Grundgeiger concluded that three aspects were decisive in creating a reliable simulation: (a) fidelity, that is, “the apparent realism of the investigative context in relation to the domain itself”; (b) control, that is, “the measures taken to ensure that the conclusions of an investigation are specific and logically defensible”; and (c) potential generalizability, that is, “the potential for depth of insight and breadth of application of conclusions” [81] (p. 87). These aspects will be carefully controlled in developing our SG and in any further investigation of it.

Our research project has various limitations, some linked to the general use of SG and others specific to SGTRI. The general elements have to do essentially with the use of human-machine interaction to simulate human-human interaction. For example, the current status of SG technology requires that some forms of interaction, such as verbal exchanges, be reduced or even eliminated completely in favor of other forms of interaction, such as written exchanges. Moreover, SG limit sensorial interactions to sight and hearing, whereas the real triage process involves all of the senses. As for the limitations specific to SGTRI, our SG presents a series of static situations that do not evolve over time and reduces the complexity of triage by removing elements, such as patient flow management and the re-evaluation of complex cases. Furthermore, distractors and environmental configurations can vary widely across ED, and *SGTRI* might not be representative of the layout of triage desks. These limitations are the consequences of both technical limitations and deliberate choices to focus our SG on a few but well defined and structured elements: patient evaluations and the influence of external distractors on the triage process.

*SGTRI* also presents a number of strengths. First, it offers a flexible instrument that can be easily tailored to numerous research projects, whether on the effects of distractors or other subjects, such as the effects of tiredness or the impact of nurse sociodemographic and professional characteristics on triage. Second, in education, it offers an efficient means of easily and quickly updating the knowledge of triage nurses. Unlike other training approaches, SG can provide a very large number of nurses with individualized and flexible training that can be adapted to their needs and requirements by, for example, modulating or controlling the level of difficulty or the amount of time to spend on each training session. Although the use of technology-enhanced simulation to train ED healthcare professionals is an innovative solution, authors underscore the importance of applying a rigorous methodology and outcome measures when using technology in the simulation field [82]. Numerous studies that have evaluated the effectiveness of SG using different outcome measures (e.g., clinical decision-making and cognitive and perceptual effects) [83–85] have found them to be reliable tools when robust methodologies, designs, and outcome measures are used. In this context, the results of our pilot study will provide useful information to test and improve our SG, our research hypotheses, and our methodology.

